#### Work disability

Subjects who work will be asked to complete the following survey item: "During the past four weeks, how many days did back pain keep you from going to work?" A response section will allow for two digits and instructions will specify to record "00" if no work loss occurred.

#### Satisfaction with back care

Satisfaction with back care will be measured by responses to the following item: "Overall, how would you describe your satisfaction with the care for your back that you have received?" Likert-scale response options will include: "very satisfied," "satisfied," neither satisfied nor dissatisfied," "dissatisfied," or "very dissatisfied."

### Data management and analysis

The data will be entered into the SPSS for Windows software package (SPSS Inc, Chicago, IL) by independent research personnel using standardized formats and dual data entry to minimize keying errors. Statistical analyses will be performed using the intention-to-treat principle. Analysis of variance (ANOVA) will be the primary method of statistical analysis. This has the advantages of allowing for assessment of repeated outcome measures over time, interaction of the factors being studied, and control of important confounders if indicated. Missing values for outcome measures will be imputed using the last observation carried forward method.

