### Sample size and statistical power

The primary outcome will be change in low back pain with OMT during the trial as measured by repeated visual analogue scale (VAS) scores for pain over 12 weeks. Based on recruitment and enrollment in the North Texas Chronic Low Back Pain Trial [12], 488 subjects was a feasible sample size target for the period August 2006 through June 2010. In a meta-analysis of the efficacy of OMT for low back pain, an effect size of 0.26 was observed for OMT vs. active treatment or placebo control [14]. Thus, using this assumed effect size, type I and type II error rates of 0.05 and 0.20, respectively, 244 subjects assigned to receive OMT (in either Group A or Group C) and 244 subjects assigned to receive sham OMT (in either Group B or Group D), the estimated statistical power of the trial for this pain outcome is 82%. For the secondary outcomes based on widely used research instruments (i.e., the Roland-Morris Disability Questionnaire [RMDQ] and the Medical Outcomes Study Short Form – 36 [SF-36] Health Survey), a total sample size of 488 will provide statistical power greater than 95% in detecting clinically relevant outcomes (a 2-point difference between groups on the RMDQ [25] and a 10-point difference between groups on the SF-36 general health scale [26]) with OMT.

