### Baseline data collection

Baseline data will be collected at the clinical screening visit prior to randomization. This includes sociodemographic data, insurance status, and a VAS for low back pain, which serves as the primary outcome measure. Other baseline measures include back-specific functioning (RMDQ), generic health status (SF-36), work disability, and back-specific satisfaction, as these are secondary outcome measures that address the four remaining recommended domains of patient-based outcomes in evaluating the treatment of spinal disorders [34]. Repeated measures of the primary and secondary outcome variables will be performed during the trial as indicated in Table 1. Additional data relevant to low back pain, medical comorbidities, and other co-treatments will also be collected.

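### Covariate control in the primary ANOVA is conditional, and screening VAS is not fixed as a covariate although every subject has it: a free gain in precision is left unused

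*Protocol article*

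**What the plan says.** Under Sample size and statistical power, the protocol article defines the endpoint: "The primary outcome will be change in low back pain with OMT during the trial as measured by repeated visual analogue scale (VAS) scores", followed over 12 weeks. Power is then computed as a plain two-group comparison of 244 against 244 subjects, and the stated result is 82%. No baseline correlation enters that calculation.

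Under Data management and analysis: "Analysis of variance (ANOVA) will be the primary method of statistical analysis". The advantages claimed for it are that it handles repeated measures, the interaction of the two factors, and "control of important confounders if indicated". The section does not say which variables count as important, what would indicate control, or when that would be decided.

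Under Baseline data collection: "Baseline data will be collected at the clinical screening visit prior to randomization". VAS pain is among those data, and Table 1 marks VAS in the pre-randomization column. Table 1 marks it again at week 0, in the same column as randomization and the first allocated treatment.

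**The concern.** Two things are at stake, and both can be settled by wording.

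The first is precision. Subtracting the baseline score fixes its coefficient at one. Adjusting for it lets the data estimate the coefficient, and in large samples the resulting variance is never larger than that of the change score. Screening VAS is already collected on everyone, so the gain costs no subjects and no visits.

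The second is prespecification. In a randomized comparison any baseline imbalance is due to chance. A rule that adjusts only when this seems called for can make the primary p-value depend on a model chosen after the data are seen.

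**Working it through.** **Inputs from the protocol article** (Sample size and statistical power)
- Effect size: "an effect size of 0.26 was observed for OMT vs. active treatment or placebo control". The SD it is scaled on is not given.
- Error rates: "type I and type II error rates of 0.05 and 0.20, respectively". Sidedness is not stated.
- n = 244 per margin.

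**Assumed, because the article does not give it:** ρ, the correlation of baseline with follow-up VAS, over 0.3 to 0.7. Variances are taken as equal at both times, with one follow-up score.

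**1. Reproduce the stated power.** With standardized effect d and relative residual SD s, the expected test statistic is d / (s·√(2/n)). With s = 1 it is 0.26 / √(2/244) = 2.872. Two-sided power at α = 0.05 is Φ(2.872 − 1.960) = 81.9% (noncentral t: 81.8%). The stated 82% is reproduced. One-sided testing gives 89.0% and does not match, so the plan's figure is two-sided with no covariate.

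**2. Relative variances.** With the post-score variance set to 1:
- change score: 2(1 − ρ)
- baseline-adjusted (ANCOVA): 1 − ρ²
- ratio of ANCOVA to change score: (1 − ρ²) / [2(1 − ρ)] = (1 + ρ)/2

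**3. Power if 0.26 is in change-score SD units.** Change-score ANOVA has 81.9%. For ANCOVA, s = √((1 + ρ)/2).

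| ρ | variance ratio | expected statistic | ANCOVA power |
|---|---|---|---|
| 0.3 | 0.65 | 3.562 | 94.5% |
| 0.5 | 0.75 | 3.316 | 91.2% |
| 0.7 | 0.85 | 3.115 | 87.6% |

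**4. Power if 0.26 is in post-score SD units.** An unadjusted comparison of post scores has 81.9%.

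| ρ | change score: variance, power | ANCOVA: variance, power |
|---|---|---|
| 0.3 | 1.40, 68.0% | 0.91, 85.3% |
| 0.5 | 1.00, 81.9% | 0.75, 91.2% |
| 0.7 | 0.60, 96.0% | 0.51, 98.0% |

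**5. If 0.26 is already a baseline-adjusted effect size**, ANCOVA power is the stated 82% and nothing is gained over that figure.

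**6. Does the ordering survive repeated scores?** Table 1 has six VAS scores after week 0. For their mean under compound symmetry (assumed), let v = (1 + 5ρ)/6. The change-from-baseline variance is v + 1 − 2ρ and the ANCOVA variance is v − ρ². The ratios are 0.327/0.817 = 0.40, 0.333/0.583 = 0.57 and 0.260/0.350 = 0.74 at ρ = 0.3, 0.5 and 0.7. The direction is the same. The power figures in steps 3 and 4 do not carry over to this case.

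**7. Bound on the open choice.** Suppose the more favourable of change-score ANOVA and ANCOVA were always reported. Simulating the two correlated test statistics under the null gives a type I error of 0.077, 0.074 and 0.068 at ρ = 0.3, 0.5 and 0.7, against a nominal 0.05. This is a worst case and not something the protocol plans.

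**The case against.** A reader might infer that the protocol adjusts for baseline pain only when imbalance appears. It does not say so. The conditional words concern important confounders, and the sentence does not mention baseline pain. Since the endpoint is change on repeated VAS, baseline probably already enters, by subtraction or as a level of the repeated measure. The loss is therefore relative to ANCOVA, not to an analysis that ignores baseline. Nor does the text say that covariates will be picked after looking at balance; it only fails to exclude this.

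A reader might also infer that the trial is underpowered or its power misstated. The 82% reproduces and meets the plan's own type II error of 0.20. Change-score ANOVA and ANCOVA are both unbiased under randomization, so the choice between them is one of efficiency.

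It can fairly be added that this is a journal article and that the covariate list may stand in an analysis plan not shown. That is why the absence of a list is not the complaint. The complaint is the conditional rule that the article does state, together with a more efficient method that the collected data already allow. The objection also stands on size: neither ρ nor the SD behind 0.26 is documented, so no single gain can be claimed.

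**Conclusion.** The point holds as a free improvement, not as an error in a stated figure. Covariate control is left conditional without a rule, and screening VAS is not fixed as a covariate.

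For one follow-up score and ρ from 0.3 to 0.7, fixing it would move power at the same sample size from 82% to between 94.5% and 87.6% if 0.26 is in change-score SD units. In post-score units, power would move from between 68.0% and 96.0% to between 85.3% and 98.0%. If 0.26 is already baseline-adjusted, there is no gain over 82%, but a fixed rule would still close the choice of model. These sizes rest on an assumed ρ, equal variances and a single follow-up score. The direction does not depend on where ρ falls in that range.

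**What to change.** Before unblinding, replace the conditional clause in Data management and analysis with:

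> The primary VAS model, and each secondary model whose outcome has a pre-randomization measurement, includes the screening (pre-randomization) value of that outcome as a covariate whatever the observed balance; adjustment for any other covariate is a sensitivity analysis.

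Two limits on this wording are deliberate.
- **Secondary outcomes.** The rule covers only outcomes with a pre-randomization score. Table 1 schedules satisfaction with back care at weeks 4, 8 and 12 only, while Baseline data collection lists it among the baseline measures. Those two places need reconciling.
- **Week-0 VAS.** It should not be averaged into the covariate unless it is confirmed to be taken before the first treatment, which no section states. If it follows treatment, adjusting for it could remove part of the treatment effect.

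The cost is one sentence of analysis wording, with no new data, visits or subjects.

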## Methods

### Subject recruitment

Subjects will be recruited by advertising in local newspapers and by seeking referrals from local physicians and from clinics affiliated with the University of North Texas Health Science Center. Subjects with constant or intermittent low back pain for at least three months will be sought. Terms other than "chronic low back pain" to be used in recruiting subjects will include "backache," "sciatica," and "lumbago." All subjects will be volunteers who are compensated for their time and travel at each study visit. Consent will be obtained from all subjects, and participants may withdraw at any time without penalty. The flow of subjects from recruitment through randomization is presented schematically in Figure 1.

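### Last observation carried forward as the only missing-data rule biases the OMT contrast if dropout differs by arm, and dilutes a growing effect even if dropout is equal

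*Protocol article*

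**What the plan says.** Under Data management and analysis, the Protocol article states: "Missing values for outcome measures will be imputed using the last observation carried forward method". The rule covers all outcomes, and no other missing-data method appears. The same section says "Statistical analyses will be performed using the intention-to-treat principle" and "Analysis of variance (ANOVA) will be the primary method of statistical analysis", and gives the handling of repeated measures as one advantage of that method.

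The primary outcome, under Sample size and statistical power, is "change in low back pain with OMT during the trial as measured by repeated visual analogue scale (VAS) scores for pain over 12 weeks". Table 1 schedules the VAS before randomization and at weeks 0, 1, 2, 4, 6, 8 and 12. Treatment is given at weeks 0 to 8. RMDQ and SF-36 are collected before randomization and then only at weeks 4, 8 and 12.

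On withdrawal, Subject recruitment says that "participants may withdraw at any time without penalty". No expected dropout rate is given, overall or by arm. The section on placebo control treatments reports that sham OMT had some therapeutic effect in the preliminary trial, and the section on the protocol and timetable allows usual care.

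**The concern.** Carrying the last score forward assumes that a subject's pain stays where it was when the subject left. The article gives two reasons to expect otherwise in both arms: an active-looking sham and permitted usual care. A dropout is then credited with too little improvement. If more sham than OMT subjects leave, sham looks worse and OMT gains a false advantage. If more OMT subjects leave, a real effect is hidden. The method therefore cannot be defended as conservative. If the OMT effect grows over the visits, equal dropout also shrinks it.

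The secondary outcomes are exposed too. A subject lost before week 4 has only the pre-randomization RMDQ and SF-36 to carry, and so is recorded as having no change.

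This criticises a stated method, not a detail that an article leaves to a fuller plan.

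**Working it through.** **1. The plan's own power figure.** Inputs from the article: effect size 0.26, 244 per arm, "type I and type II error rates of 0.05 and 0.20, respectively". Two-sided: 0.26 × √(244/2) = 2.872; 2.872 − 1.960 = 0.912; Φ(0.912) = 0.819. The stated 82% reproduces and is not in error. It takes 244 analysed values per arm.

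**2. Assumed inputs (not in the documents).**
- VAS SD 22 mm and within-subject correlation 0.5.
- Shared improvement of 15 mm by week 12.
- True effect either zero or 0.26 × 22 = 5.7 mm.
- Dropout random within arm, with the last observed visit equally likely at weeks 0, 1, 2, 4, 6 and 8.

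The SD of change is 22 × √(2 × (1 − 0.5)) = 22 mm, so the SE of the contrast is 22 × √(2/244) = 1.99, about 2.0 mm.

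**3. Improvement missed per dropout, linear trend, change to week 12.** The mean last visit is (0+1+2+4+6+8)/6 = 3.5 weeks. The fraction missed is 1 − 3.5/12 = 0.708. Each dropout loses 0.708 × 15 = 10.6 mm.

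**4. No true effect, linear trend.** Bias = difference in dropout × 10.6 mm.
- 10% OMT / 20% sham: 0.10 × 10.6 = 1.1 mm. Type I error = Φ(−1.96 + 1.06/2.0) + Φ(−1.96 − 1.06/2.0) ≈ 8%; simulation gives about 9%.
- 8% OMT / 23% sham: 0.15 × 10.6 = 1.6 mm; type I error about 12%.

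**5. No true effect, milder settings.**
- Improvement complete by week 4: the mean fraction reached is (0+0.25+0.5+1+1+1)/6 = 0.625, so each dropout loses 0.375 × 15 = 5.6 mm. Bias is 0.6 mm (10%/20%) and 0.8 mm (8%/23%).
- Linear trend, contrast averaged over weeks 1 to 12: the shortfalls, summed over later visits for each possible last visit, are 33, 27, 22, 14, 8 and 4 weeks. Their total of 108, divided by 6 visits and 6 last visits, is 3.0 weeks, or 3.0/12 × 15 = 3.75 mm per dropout. Bias is 0.4 mm and 0.6 mm.
- Type I error in these four cases is about 6 to 7%.

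**6. True effect 5.7 mm, linear trend, change to week 12.**
- 20% OMT / 10% sham: 5.7 − 0.20 × 0.708 × 20.7 + 0.10 × 0.708 × 15 = 5.7 − 2.93 + 1.06 = 3.8 mm. Power = Φ(3.8/2.0 − 1.96) ≈ 48%. The fair comparator is observed week-12 data with the same dropout: SE = 22 × √(1/195 + 1/220) = 2.16; power = Φ(5.7/2.16 − 1.96) ≈ 75%.
- 15% in each arm: 5.7 × (1 − 0.15 × 0.708) = 5.1 mm; power about 72%. Observed data, 207 per arm: SE 2.16, power about 75%.
- 15% in each arm with the early plateau: 5.7 × (1 − 0.15 × 0.375) = 5.4 mm; power is no lower than with observed data.

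**7. Simulation.** Simulated trials with 244 per arm agree with these results. Observed week-12 data kept type I error near 5%. Under carry-forward, the model SE and the empirical SE were both about 2.0 mm. A separate run in SD units (correlation 0.6, true effect 0.26, shared linear improvement of 0.5 or 1.0 SD, 10%/30% dropout either way) gave carry-forward estimates from 0.07 to 0.39.

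**The case against.** The strongest case against is that the harm depends on dropout that the document never quantifies. Sham subjects are treated in similar positions and all subjects are compensated at each visit, so dropout may be low and balanced. With no change over time and no OMT effect, carry-forward gave no bias in simulation. This stands: the size is conditional. But nothing in the article shows that the problem is negligible, and the article's own remarks make change over time likely.

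A second objection is that week-12 change with a linear trend is the setting most unfavourable to the rule. The outcome is defined "as measured by repeated visual analogue scale (VAS) scores for pain over 12 weeks", and the article does not say which contrast of those scores is primary. This also stands, and the milder settings in step 5 show the reduction. The direction of the bias is unchanged.

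Two stronger readings are tempting:
- A reader might infer that treating imputed values as observed makes the standard errors too small. That is a fair worry about single imputation in principle, but the week-12 simulations showed no such error. The repeated-measures ANOVA itself was not simulated.
- A reader might charge the whole fall from the planned 82% power to carry-forward. Most of the equal-dropout loss comes from the missing data: observed-data power is already 75%, and carry-forward takes it to 72%. Under an early plateau there is no net power loss.

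Finally, a mixed model rests on missing at random, which cannot be tested. That is true, but it is a weaker demand than assuming that pain freezes at withdrawal.

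**Conclusion.** The concern holds as a conditional bias. Carry-forward as the sole rule misstates the change of dropouts whenever scores move. It then shifts the OMT contrast either way if dropout differs by arm, and dilutes a growing effect even if dropout is equal.

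Under the assumptions in step 2, 10 to 15 points more dropout on sham gives a false OMT benefit of 0.4 to 1.6 mm and type I error of roughly 6 to 12%, depending on trajectory and contrast. The largest power cost shown is 48% against 75%, with 20% OMT / 10% sham dropout and a linear trend. With equal 15% dropout the cost is small: dilution from 5.7 to about 5.1 mm, with power 72% against 75%.

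The stated 82% power is correct on its own inputs, and no fault in the standard errors was shown.

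**What to change.** Replace the carry-forward sentence with a primary analysis along these lines: a likelihood-based mixed model for repeated measures on all observed post-baseline VAS scores, with the two treatment factors, visit as a category and their interactions, baseline VAS as a covariate and an unstructured covariance; valid under missing at random; no single imputation. Use the same model for RMDQ and SF-36 general health. Keep last observation carried forward only as a sensitivity analysis. Make the change before unblinding, so that the method is not chosen after dropout by arm is known.

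The cost is wording and slightly more analysis work, plus explicit reliance on the missing-at-random assumption. No new data, visits or subjects are needed.

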## Ethical aspects

The study protocol was approved by the Institutional Review Board (IRB) of the University of North Texas Health Science Center prior to implementation. The IRB will continue to monitor the study regularly. Additionally, a Data Safety and Monitoring Board (DSMB) has been established, and will closely monitor the study for the occurrence of any serious adverse events. The study was registered as a Phase III trial with ClinicalTrials.gov in April 2006 (ClinicalTrials.gov identifier, NCT00315120).

## Conclusion

To the best of our knowledge, if successfully completed as described herein, the OSTEOPATHIC Trial will be the largest randomized controlled trial involving OMT. It will provide long awaited primary data on the efficacy of OMT and UPT for chronic low back pain.
